### Subgroup and heterogeneity analysis plan

The primary subgrouping is based on baseline FSH level according to the APHRODITE classification:
Group 3: FSH 7.6–12.0 IU/LGroup 4: FSH >12.0 IU/LThe purpose of a subgroup analysis is to assess whether the treatment effect on the primary endpoint—sperm available for ICSI by Week 16—differs between APHRODITE Groups 3 and 4.

#### Statistical model and test of interaction

The analysis will be interaction-driven. Treatment effects within subgroups will be descriptive unless the treatment-by-subgroup interaction is statistically significant.

A generalized linear model (identity link, robust standard errors) shown in Equation 1 will be used:$$Y\_i\;=\beta_{0\;}+\beta_{1}\cdot \mathrm{Treatment}\_i+\beta_{2}\cdot \mathrm{Group}\;4\_i+\beta_{3}\cdot (\mathrm{Treatment}\_i\times \mathrm{Group}\;4\_i)+\gamma^{T}X\_i+u\_\mathrm{site}+\varepsilon \_i,$$(1)where Y_i represents the binary composite outcome (sperm available for ICSI by Week 16), Group 4_i is an indicator variable for APHRODITE Group 4, and X_i denotes prespecified covariates (female age, male age, center, baseline semen parameters, baseline TT/E2, baseline DNA Fragmentation Index (DFI), and number of Metaphase II (MII)). The interaction term *β*_3_ tests for a differential treatment effect between Groups 3 and 4. Random intercepts for site will account for clustering, and results will be presented as marginal risk differences.

The test for interaction will use a two-sided *α* = 0.05. Although prospectively specified and biologically motivated, subgroup analyses are considered supportive and hypothesis-generating unless sufficiently large interaction effects are observed. The trial is primarily powered for the overall treatment effect rather than formal interaction testing. The Table 3 illustrates SPIRIT schedule for enrollment, intervention, and assessments.

**Table 3 T3:** SPIRIT schedule of enrollment, interventions, and assessments.

Procedure/time point	Enrollment (≤28 days)	Baseline (W0)	W12	W16
Eligibility and consent	X			
Randomization		X		
hCG + FSH (Arm A)		X	X	X
Endocrine labs (TT, E2, LH, FSH; CBC/Hct, LFTs, lipids)		X	X	X
Semen analysis		X	X	X
Micro-TESE (if needed)				X
AE/SAE assessment		X	X	X

#### Reporting and visualization

Forest plots will display risk differences (treatment − control) with 95% confidence intervals for the overall population and for each subgroup. The interaction *p*-value will accompany the forest plot. A Supplementary Figure will show treatment effect as a function of continuous FSH modeled with restricted cubic splines (three to four knots) and 95% confidence bands.

#### Multiplicity control

This is the only prespecified effect-modification test. All other subgroup analyses (e.g., testosterone level and age strata) are exploratory and will be labeled accordingly. No alpha adjustment is required provided only this single interaction is tested. If additional interactions are introduced, family-wise error rate will be controlled using the Holm procedure.

#### Sensitivity analyses

Continuous FSH model using restricted cubic splines.Mixed-effects logistic regression with logit link; marginal effects reported as risk differences.Per-protocol and as-treated analyses repeating the interaction test.Center robustness: treatment ×   subgroup ×   center term explored if strong site heterogeneity is suspected.

#### Power considerations

Subgroup and interaction analyses are less powered than main effects. With approximately 860 participants in total (≈425 per arm) and an SOC success rate of 40%, the study will have sufficient power to detect large interactions (≥10 percentage-point difference in treatment effects between Groups 3 and 4). Smaller differences will be interpreted cautiously and only in the context of consistent secondary outcomes.

Assumptions: Control 40%, Treatment 50% (Δ = +10%); two-sided *α* = 0.05; power 80%; and dropout 10%.

Unpooled normal approximation: n_per_arm = ((1.96 + 0.84)^2^ × [0.45 × 0.55 + 0.55 × 0.45])/(0.10)^2^ ≈ 388 per arm predropout. Inflated by 10% → 427; plan 430 per arm (860 total) for conservative rounding and operational ease. Consider +3%–5% if center heterogeneity or attrition >10%.

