### Sample size estimation

The sample size calculation assumed a control-group success rate of approximately 40%, based on contemporary literature evaluating sperm retrieval outcomes in idiopathic NOA (1, 7). The study was powered to detect an absolute improvement of approximately 10 percentage points in the primary composite endpoint with two-sided *α* = 0.05 and 80%–90% statistical power using a 1:1 allocation ratio. The planned total sample size also accounted for anticipated attrition, intercenter variability, and preservation of reasonable power for the prespecified interaction analysis between APHRODITE Groups 3 and 4.

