#### Efficacy analysis

**Primary analysis:** Compare proportions at Week 16 between arms using a risk difference and risk ratio with 95% CIs (Wald/Newcombe). The primary efficacy analysis will use a mixed-effects generalized linear model including a treatment arm and the APHRODITE group as fixed effects and the study site as a random intercept to account for clustering by center. A log-binomial mixed model will be preferred for estimating adjusted risk ratios. If convergence issues occur, a modified Poisson mixed-effects model with robust variance will be used as a prespecified alternative. The modified Poisson approach is specified solely as a fallback method in the event of log-binomial model non-convergence and does not represent a separate primary analytical method.**Sensitivity analyses:**
•**Time**-**to**-**event** (Cox model; log-rank) for time to first sperm availability.•**Per**-**protocol** analysis excluding major deviations.•**Tipping**-**point** analyses for missing outcomes.**Subgroups (prespecified):** APHRODITE Group 3 vs. 4, site, baseline TT strata (<250 vs. 250–349 ng/dL), age (<35 vs. ≥35), varicocele grade (<3 vs. 3). Interaction terms to assess heterogeneity.**Multiplicity:** Secondary endpoints reported with 95% CIs; no formal alpha allocation unless specified in a hierarchical plan.**Handling intercurrent events:** Treatment policy (analyze as randomized). For couples without ART attempts by Week 16, embryologic/reproductive endpoints treated as not evaluable; no imputation for primary endpoint beyond the landmark rule.

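### The plan says 860 men suffice to detect a 10-point treatment-by-APHRODITE interaction; with an equal Group 3/4 split the power is about 32%, and 80% is reached only near 19 points

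*Protocol article*

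**What the plan says.** Under Power considerations the protocol starts from this premise: "With approximately 860 participants in total (≈425 per arm) and an SOC success rate of 40" per cent. It then concludes that "the study will have sufficient power to detect large interactions (≥10 percentage-point difference in treatment effects between Groups 3 and 4". Only differences smaller than that are to be read with caution. Sample size estimation lists, among the things the total N allowed for, "preservation of reasonable power for the prespecified interaction analysis between APHRODITE Groups 3 and 4".

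Other statements pull the other way. Statistical model and test of interaction says: "The trial is primarily powered for the overall treatment effect rather than formal interaction testing". Power considerations itself opens by conceding that interaction analyses have less power than main effects.

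The test is well defined. The model is described as "A generalized linear model (identity link, robust standard errors", with the treatment-by-Group 4 coefficient as the quantity tested, and "The test for interaction will use a two-sided *α* = 0.05".

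On the number of such tests, Multiplicity control says of the APHRODITE interaction: "This is the only prespecified effect-modification test". It labels other subgroup analyses exploratory and invokes Holm if interactions are added. Efficacy analysis lists five prespecified subgroups (APHRODITE group, site, baseline testosterone, age, varicocele), ending with "varicocele grade (<3 vs. 3). Interaction terms to assess heterogeneity".

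**The concern.** The only calculation shown sizes the trial for a 10-point difference between arms. An interaction is a difference between two such differences, each estimated in part of the sample. With equal groups its standard error is about twice that of the overall effect. A sample that gives roughly 80% power for a 10-point main effect cannot give comparable power for a 10-point interaction.

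What is at stake is how the APHRODITE result is read. Subgroup effects stay descriptive unless the interaction is significant, and the rule on cautious interpretation starts only below 10 points. A reader who relies on the power sentence would think a 10-point difference between Groups 3 and 4 was well within the trial's reach.

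**Working it through.** **Inputs.**
- Control 40%, treatment 50%, two-sided alpha 0.05, 80% power, 860 men planned as 430 per arm (Power considerations, which also says about 425 per arm).
- Identity link, so the interaction is a difference in risk differences (Statistical model and test of interaction).
- Allocation 1:1, stratified by APHRODITE group (Randomization and masking).
- Missing primary outcomes count as failures (Interim analysis and sample estimation), so all 860 are analysed.
- Group 3/4 split: not given. I assume 50:50 and show the range to 80:20.

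**The plan's own figure.** (1.96 + 0.84)² × [2 × 0.45 × 0.55] / 0.10² = 7.84 × 0.495 / 0.01 = 388 per arm. Then 388 × 1.10 = 427, rounded to 430. This reproduces, and power for the main effect at 430 per arm is about 84%. No interaction term enters the calculation.

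**Interaction, equal split.** There are four cells of 860/4 = 215. An average effect of 10 points with a 10-point interaction means 40% to 55% in one group and 40% to 45% in the other.

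- Sum of p(1−p) = 0.40×0.60 + 0.55×0.45 + 0.40×0.60 + 0.45×0.55 = 0.975
- SE = √(0.975/215) = 0.0673, against √(0.49/430) = 0.0338 for the main effect
- Power = Φ(0.10/0.0673 − 1.96) = Φ(−0.475) ≈ 0.32; a simulation of 200,000 trials gives 31.6%
- Difference detectable with 80% power = 2.80 × 0.0673 = 0.188, about 19 points
- Smallest estimate that reaches significance = 1.96 × 0.0673 = 0.132. An observed 10-point interaction would have a 95% CI of about −3 to +23 points.

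**Interaction, 80:20 split.** Cells are 344 and 86 per arm. Keeping the average effect at 10 points, the treated rates are 48% in the larger group and 58% in the smaller.

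- SE = √[(0.24 + 0.2496)/344 + (0.24 + 0.2436)/86] = 0.0839
- Power ≈ 0.22
- Detectable with 80% power = 2.80 × 0.0839 = 0.235, about 24 points

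The result is the same whichever group is the larger.

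**More and less favourable variants** (10-point interaction; equal split unless stated):

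| Variant | Power |
|---|---|
| 860 analysed | 32% |
| 850 analysed (425 per arm) | 31% |
| 774 analysed (10% lost) | 29% |
| 860, split 70:30 | 28% |
| 1,032 analysed (the +20% re-estimation cap) | 37% |
| Covariates remove 30% of variance | 43% |
| Covariates remove 50% of variance | 56% |
| One-sided 0.05 | 44% |

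None reaches 80%. For scale, 80% power at 10 points with an equal split needs 4 × 0.975 × 2.80² / 0.01, about 3,060 men, or roughly 3.6 times the plan.

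**The case against.** The best defence is that the protocol already limits the weight of this analysis. It calls the subgroup work supportive and hypothesis-generating, says the trial is powered mainly for the overall effect, and plans forest plots with confidence intervals for each subgroup plus subgroup estimates in the main results table. The 32% also depends on a split the protocol does not state and ignores covariate adjustment, which the model includes.

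Much of this stands. It lowers the severity and means that the figures must be quoted with their assumptions. It does not rescue the sentence. The caveats sit beside a specific claim of adequacy at 10 points and contradict it without correcting it. The assumptions also do not favour the criticism: the equal split is close to the best case, and a generous covariate gain still leaves power well under 80%.

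A reader might infer more than the document supports:

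- *That the plan will take a non-significant interaction as proof that Groups 3 and 4 respond alike.* No section sets that rule, and subgroup estimates are reported either way. The misreading is possible but not planned.
- *That five interaction tests carry an uncontrolled error of 1 − 0.95⁵, about 23%.* That presumes five independent, unadjusted tests. Multiplicity control labels the others exploratory and provides Holm if interactions are added. What stands is that it names one prespecified test, while Efficacy analysis lists five prespecified subgroups with interaction terms.
- *That the grade 3 varicocele stratum must be empty.* This follows from Population and Table 2, which exclude grade 3 and above. But the prose of Study design and methods excludes untreated clinical varicocele requiring correction, and the abstract refers to clinically significant varicocele. The document shows a conflict, not which wording governs.

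**Conclusion.** The statement of sufficient power is wrong as written, and the claim that the total N preserved reasonable interaction power has no calculation behind it. The protocol does not quantify its claim, but its own standard in the same section is 80%. Against that, a true 10-point interaction would be missed about two times in three under an equal split with all 860 analysed and no covariate gain, and nearly four times in five at 80:20. The 19- and 24-point figures rest on the same assumptions and on a 40% control rate in both groups.

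Severity is moderate. The error concerns the interpretation of a supportive analysis. The primary comparison, its alpha and the main-effect sample size are not touched.

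**What to change.** 1. **Power considerations.** Replace the sentence on sufficient power with text such as: *With 860 men analysed, a control rate of 40%, no allowance for covariates and equal numbers in Groups 3 and 4, power for a 10-point interaction is about 32%, and 80% power is reached near 19 points; with an 80:20 split these are about 22% and 24 points. A non-significant interaction does not exclude a 10-point difference.* If the sponsor has an expected split, use it.
2. **Same section.** Apply the rule on cautious interpretation to differences below about 19 points (about 24 at 80:20) instead of below 10.
3. **Sample size estimation.** Delete the clause on interaction power.
4. **Multiplicity control and Efficacy analysis.** Reconcile them: either APHRODITE is the only prespecified interaction test and the others are labelled exploratory in both places, or the additional interactions are prespecified and Holm is stated to apply.
5. **Varicocele.** Reconcile the wording in the abstract, Population, Study design and methods (prose and Table 2) and the subgroup list in Efficacy analysis.

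The cost is wording only: no extra participants and no change to the primary analysis. The stated interaction power becomes less favourable.

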#### Secondary efficacy endpoints

Micro-TESE sperm retrieval success rate (SSR) among those undergoing surgery.Need for surgical sperm retrieval (any micro-TESE performed by Week 16).Time to first sperm availability (ejaculation or micro-TESE), from randomization.Embryological outcomes: ICSI fertilization rate, blastulation rate, blastocyst quality, and top-1-quality blastocyst rate (per couple cycle).Reproductive outcomes: Clinical pregnancy and miscarriage rates per embryo transfer; live birth (exploratory).

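### The interaction section states two conflicting gates for a Group 3 versus Group 4 claim, and a 10-point difference, called large and adequately powered, is neither significant at 860 men nor detectable with more than about 32% power

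*Protocol article*

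**What the plan says.** All of this is in the protocol article, under the subgroup and heterogeneity analysis plan.

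- **Statistical model and test of interaction.** The section opens with a clear gate: "Treatment effects within subgroups will be descriptive unless the treatment-by-subgroup interaction is statistically significant". The level is fixed: "The test for interaction will use a two-sided *α* = 0.05". A sentence later comes a different condition: "subgroup analyses are considered supportive and hypothesis-generating unless sufficiently large interaction effects are observed". No threshold is given for sufficiently large. The section adds that the trial is powered mainly for the overall effect.
- **Power considerations.** The planned 860 participants are said to give "sufficient power to detect large interactions (≥10 percentage-point difference in treatment effects between Groups 3 and 4"). No power figure and no group split are stated. The next sentence deals with anything below that size: "Smaller differences will be interpreted cautiously and only in the context of consistent secondary outcomes". It does not name the outcomes or say what counts as consistent.
- **Secondary efficacy endpoints.** The list begins with "Micro-TESE sperm retrieval success rate (SSR) among those undergoing surgery". It continues with need for surgery, time to first sperm availability, embryological outcomes and reproductive outcomes. The Outcomes section calls the last two groups exploratory.

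**The concern.** A significance gate and an observed-size gate can give different answers on the same data. If the observed interaction is large but not significant, one sentence keeps the subgroup effects descriptive and another removes the hypothesis-generating label. The only size the document attaches to large is 10 points, and caution is asked for only below it, so a reader could take 10 points as enough.

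The sufficient-power statement reinforces that reading: if the trial were well powered at 10 points, an observed 10-point gap would normally be significant. The secondary-outcome clause then offers support for smaller gaps from a list in which two outcomes are built from the primary events.

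At stake is the interpretation of the one prespecified effect modifier. Subgroup estimates go into the main results table (Operational considerations), and the Discussion expects the trial to guide more personalised care. A chance difference between Groups 3 and 4 could be presented as more than chance without breaking any sentence of the plan.

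**Working it through.** **Inputs from the document.** 430 men per arm, 860 in total; control 40%, treatment 50%; two-sided 0.05; 1:1 allocation. Missing primary outcomes count as failures, so all 860 stay in the analysis.

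**Assumption.** The share of men in Group 4 is not given. I use 50% (best case), 70% and 80%.

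**1. The plan's own figure.** (1.96 + 0.84)² × (0.45 × 0.55 + 0.55 × 0.45) / 0.10² = 7.84 × 0.495 / 0.01 = 388 per arm. Adding 10% gives 427, rounded up to 430. This reproduces, but it sizes the main effect only.

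**2. Standard error of the interaction.** The interaction is the difference between two risk differences, so its variance is the sum of p(1−p)/n over four arm-by-group cells. At 50:50 each cell has 215 men. With no true interaction:

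SE = √[2 × (0.40 × 0.60 + 0.50 × 0.50) / 215] = √(0.98 / 215) = 6.75 points.

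For comparison, the main-effect SE is √(0.49 / 430) = 3.38 points. The interaction SE is twice that.

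**3. What an observed 10-point gap means at 50:50.** z = 10 / 6.75 = 1.48, two-sided p = 0.14. Significance needs 1.96 × 6.75 = 13.2 points.

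**4. Power for a true 10-point interaction.** Take effects of +5 and +15 points. SE = √[(2 × 0.24 + 2 × 0.2475) / 215] = 6.73 points. 10 / 6.73 − 1.96 = −0.475, so power is about 32%. For 80% power the true interaction must be 2.80 × 6.73 = 18.9 points. Alternatively the trial needs about 860 × (18.87 / 10)² = 3,060 men.

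**5. Other splits (860 men).**

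| Group split | SE (points) | Smallest significant gap | Chance of a gap ≥10 points, no true interaction | Power for a true 10 points |
|---|---|---|---|---|
| 50:50 | 6.75 | 13.2 | 13.9% | 32% |
| 70:30 | 7.37 | 14.4 | 17.5% | 27% |
| 80:20 | 8.44 | 16.5 | 23.6% | 22% |

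The blinded re-estimation may add at most 20%. At 1,032 men and 50:50 the SE is 6.75 / √1.2 = 6.16 points; a 10-point gap still has p of about 0.10, and power is about 37%.

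**6. The secondary-outcome clause.** I rely on simulated trials (40,000 per scenario, 860 men). The article gives no ejaculate rates, so 5%, 10% and 20% were assumed in Arm A and 2% in standard of care. The 5-to-10-point band below is illustrative; the document sets no lower limit. Results are for a 50:50 split.

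| Secondary outcome | Correlation of its interaction with the primary one | Same direction when the chance gap is 5–10 points | Same direction for a 5–10-point gap under a true 10-point interaction |
|---|---|---|---|
| Micro-TESE retrieval rate | 0.92–0.98 | 99–100% | 99–100% |
| Availability by Week 16 (proxy for time to availability) | about 1.00 | 100% | 100% |
| Need for surgery | 0.20–0.38 | 55–65% | 60–78% |
| Fertilization or pregnancy rate given sperm (simulated as independent) | about 0 | about 50% | about 50% |

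For the first two rows, agreement is as frequent without a true interaction as with one, so it does not help to tell the two apart.

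**The case against.** **The clauses restrict rather than license.** The sentence on smaller differences adds a condition and asks for caution, the opening gate of the interaction section still stands, and the forest plot will carry confidence intervals and the interaction p-value. This is fair. Nowhere does the document say that a non-significant gap will be reported as established effect modification, and a reader who infers that goes beyond the text.

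**The 10 points may be only a design alternative.** The interaction section never ties sufficiently large to 10 points, and the power section uses that figure for an interaction to be detected. It could also mean large enough to be significant. So the 14–24% is the error rate of one possible reading, not of the stated test, which keeps its 5%. But on the design-alternative reading the sufficient-power claim is wrong instead, at 22–32%. If the clause means no more than significance, it is redundant.

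**Not all secondary outcomes overlap.** Correct. A reader might infer that the whole list counts the same successes. Only the retrieval rate and time to availability do; need for surgery is weakly related, and fertilization and pregnancy rates have different events and denominators. Nor does overlap explain the weakness of the size exception, which comes from the standard error.

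**Size is not worthless as evidence.** Also correct. At 50:50 a gap of at least 10 points appears in about 14% of trials with no interaction and about 50% with a true 10-point interaction. To say that size cannot separate the two would be too strong.

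**Covariate adjustment could sharpen the estimate.** For a 10-point gap to be significant at 50:50 the SE must fall to 5.10 points, a variance reduction of 1 − (5.10 / 6.75)² = 43%. Eighty per cent power needs 1 − (3.57 / 6.73)² = 72%. The document gives no basis for either.

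**Conclusion.** The point holds in limited form. The interaction section gives two conditions that can disagree, and the power statement beside them is not supported by the plan's own inputs. In the best case for group split, a 10-point interaction has about 32% power and an observed 10-point gap has p of about 0.14; at 80:20 power is about 22%. The secondary-outcome clause is weak where it would rest on micro-TESE retrieval rate or time to sperm availability, and only there is shared events the reason.

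These figures rest on the plan's 40% and 50% rates, all 860 men analysed, an unadjusted normal approximation and an assumed group split. The overlap results also rest on assumed ejaculate rates. The damage is confined to how a subgroup difference is interpreted. The primary analysis, the main-effect sample size and the 5% level of the interaction test itself are not affected.

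**What to change.** Three wording changes:

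1. In the section on the statistical model and test of interaction, end the hypothesis-generating sentence before its exception for sufficiently large effects, so that the interaction test is the only gate.
2. In Power considerations, replace the sufficient-power claim with the actual power for a true 10-point interaction: about 22–32% depending on the group split, with about 19 points needed for 80% power at 50:50.
3. Replace the sentence on smaller differences with: *An interaction that is not statistically significant, whatever its observed size, is reported with its 95% CI as hypothesis-generating; agreement with micro-TESE SSR or time to sperm availability is not treated as independent corroboration because these share the primary outcome events.*

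The changes need no extra participants, data or analyses. The sponsor gives up the option of promoting a non-significant subgroup difference on its size or on overlapping outcomes. The wording should be settled before outcome data by arm are seen.
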